#### Sample size calculation

The sample size was determined according to a power calculation using a dichotomous variable: meeting the PA guideline with at baseline 50% not meeting the guideline and after the intervention 40% (intervention group) vs 50% (in control group). Based on these numbers, and 80% power and significance of 0.05, 775 employees are required at the 12-month follow-up with 387 in control group and 387 in intervention group. Thus, assuming that approximately 20% of participants will be lost to follow-up at 12 months, we will aim to recruit 928 employees at baseline and allocate 424 to the intervention and control groups (Figure 1).

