### Step 6: Evaluation plan

#### Study design

The intervention as developed in the previous steps will be evaluated in a cluster-randomised controlled trial in South African worksites with a 12-month follow-up. The two intervention groups will receive 6 counselling sessions over either a 3 or 6-month period, described in Table 3. The control group will receive usual care. These participants will be unaware of the other two groups participating in the research study.

**Table 3 T3:** Timeline and contact schedule for employees in the intervention groups

**Week**	**6-month intervention group**	**3 month intervention group**
0	Wellness day at company. (Baseline measurement)	Wellness day at company. (Baseline measurement)
1	Face-to-face contact	Face-to-face contact
	(set goals, action plan)	(set goals, action plan)
4	Telephone contact	Telephone contact
	(monitor progress)	(monitor progress)
8	Telephone contact	Telephone contact
	(monitor progress)	(monitor progress)
12	Telephone contact	Face to face (final contact)
	(monitor progress)	
16	Telephone contact (monitor progress)	
20	Telephone contact	
	(monitor progress)	
24	Face to face (final contact)	
	(set new goal, plan way forward)	
26	First follow up measurement	
52	Second follow up measurement	First follow up measurement Second follow up measurement

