#### Randomisation

Randomisation will take place at the company level, where participating companies will be assigned to either the intervention or the control group. The wellness specialists’ manager will assign each company with a number and then use a random numbers table to allocate the companies to either the intervention or control.

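### The sample size treats employees as individually randomised although whole companies are randomised, so 775 completers do not give the stated 80% power

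*Protocol article*

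**What the plan says.** The Study design section says the intervention "will be evaluated in a cluster-randomised controlled trial in South African worksites with a 12-month follow-up". The Randomisation section fixes the unit: "Randomisation will take place at the company level, where participating companies will be assigned to either the intervention or the control group".

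The Sample size calculation section then works at the level of the employee. It states that "The sample size was determined according to a power calculation using a dichotomous variable: meeting the PA guideline", with half of employees not meeting the guideline at baseline and, "after the intervention 40% (intervention group) vs 50% (in control group") not meeting it. It concludes: "Based on these numbers, and 80% power and significance of 0.05, 775 employees are required at the 12-month follow-up", split as "387 in control group and 387 in intervention group". A 20% loss to follow-up then takes the recruitment target to 928.

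The calculation mentions no ICC, design effect, number of companies or number of employees per company, and the rest of the text supplies none. The only related fact is that eligible companies must be large, with about 300 employees or more (Setting; Inclusion and exclusion criteria for companies).

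**The concern.** When companies are randomised, employees of one company are not independent observations. The article itself gives reasons to expect similarity within a company. The activity questionnaire counts work-related and transport activity as well as leisure. The needs assessment describes the work environment as a barrier to activity. Management support is treated as a condition for the programme to work. Any positive ICC inflates the variance of the difference between arms, so 775 completers carry less information than 775 independent people.

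This is the trial's only sample size justification, and companies are asked to commit to a year of follow-up on the strength of it. If the real power is well below 80%, a null result could be read as an ineffective programme when the trial was too small for its own 10-point target. That reading would carry through to the cost-effectiveness conclusions meant for health care funders.

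**Working it through.** **Inputs from the article (Sample size calculation):** p1 = 0.50 (control) and p2 = 0.40 (intervention) not meeting the guideline; alpha 0.05; power 80%; equal arms. Sidedness is not stated; two-sided reproduces the figure.

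**Step 1: reproduce the stated size.** For independent individuals, with pooled p = 0.45:

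n per arm = [1.96 × √(2 × 0.45 × 0.55) + 0.8416 × √(0.25 + 0.24)]² / 0.10²
= [1.379 + 0.589]² / 0.01 = 387.3

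Total = 2 × 387.3 = 774.7, against 387 per arm and 775 stated. The alternatives fit worse: one-sided gives 305 per arm, and a continuity correction gives 408. The implied design effect is 775 / 774.7 = 1.00, so no inflation for clustering is hidden in the number.

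**Step 2: add the clustering.** With K companies in total and equal numbers in each:

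- m = 775 / K completers per company
- DE = 1 + (m − 1) × ICC
- effective n per arm = 387.5 / DE
- power = Φ{[0.10 × √(effective n) − 1.379] / 0.70}, where 0.70 = √(0.25 + 0.24)

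K and ICC are **assumptions**, because the article gives neither. Worked case, K = 20 and ICC 0.02: m = 38.75; DE = 1 + 37.75 × 0.02 = 1.755; effective n = 220.8; power = Φ[(1.486 − 1.379) / 0.70] = Φ(0.153) = 56%.

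Power for 50% v 40% with 775 completers:

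| Companies | ICC 0.01 | ICC 0.02 | ICC 0.05 |
|---|---|---|---|
| 10 | 56% | 42% | 25% |
| 20 | 66% | 56% | 38% |
| 30 | 71% | 63% | 46% |

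**Step 3: allow for few companies.** The normal approximation is optimistic when there are few clusters. Simulated beta-binomial data, analysed by a t-test on company means (4,000 replicates), gave lower power in every cell:

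| Companies | ICC 0.01 | ICC 0.02 | ICC 0.05 |
|---|---|---|---|
| 10 | 46% | 33% | 21% |
| 20 | 61% | 52% | 36% |
| 30 | 67% | 61% | 44% |

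**Step 4: what 80% power would need.** Required completers = 775 × DE. At 50 completers per company:

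- ICC 0.01: DE = 1 + 49 × 0.01 = 1.49, so 1,155 completers
- ICC 0.02: DE = 1 + 49 × 0.02 = 1.98, so 1,535 completers

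Over ICC 0.005 to 0.05 and 10 to 100 completers per company, the requirement runs from 810 to 4,612 completers, and the power of 775 completers runs from 78% down to 21%.

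**Step 5: what 928 recruits give.** At the article's 20% loss, 928 × 0.8 = 742 completers. At ICC 0.02 this gives about 41% power with 10 companies and 62% with 30, against 42% and 63% on 775.

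**The case against.** The core is hard to contest. The figure reproduces without a design effect, so it cannot be defended as a detail that a condensed article leaves to a fuller protocol. The flow diagram, which is not shown here, might give the number of companies, but it could not change how 775 was obtained.

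Four objections deserve weight.

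- **The size of the shortfall is assumed.** This stands. At ICC 0.005 the power is about 75% with 30 companies and 78% with 60; at ICC 0.001 with 20 companies it is between 78% and 79%. The document supports below 80% by an unknown amount, not one particular figure. These cases shrink the loss without removing it.
- **The percentages describe one comparison.** They apply to an unadjusted binary comparison at 12 months, as in the article's own calculation. The stated primary outcome is a change in habitual activity, compared by ANOVA, and its power could differ in either direction. This stands as a limit on how the tables may be read.
- **Baseline adjustment could recover precision.** It could, but the sample size calculation neither plans nor uses it.
- **Shared influences within a company are only partly documented.** A common worksite and management are reasonable inferences. Nothing says that one counsellor serves one company, and control employees receive no counselling. The argument needs only a positive ICC from some source.

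**Conclusion.** The sample size paragraph is wrong as written. The trial randomises companies, the stated 775 is the size for an individually randomised trial, and its 80% power holds only if the ICC is zero. That conclusion follows from the article's own numbers and needs no assumption about the ICC beyond its being positive.

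The amount lost does rest on assumptions. For 10 to 30 companies and ICC 0.01 to 0.05, power lies between about 71% and 25% by the design-effect formula, and somewhat lower with a company-level t-test. Unequal numbers per company, which the formula ignores, would lower it further. With many companies and a very small ICC the loss is only a few points. The point must be fixed because the printed power claim does not belong to the printed design.

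**What to change.** Rewrite the Sample size calculation section so that it:

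1. states the planned number of companies and the expected number of recruits per company;
2. states an ICC range with its source;
3. multiplies the individual-level size by 1 + (m − 1) × ICC and corrects for the limited number of companies, for example by using t rather than normal quantiles with degrees of freedom based on companies;
4. reports the power, or the detectable difference, that 928 recruits give after the expected 20% loss, that is, from about 742 completers.

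As an illustration of item 4, take 20 companies and ICC 0.02: m = 742 / 20 = 37.1, DE = 1.722 and effective n = 371 / 1.722 = 215.4 per arm. The detectable difference from 50% at 80% power is then about 13.3 points: [1.96 × √(2 × 0.4335 × 0.5665) + 0.8416 × √(0.25 + 0.367 × 0.633)] / √215.4 = 1.958 / 14.68 = 0.133.

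This costs one paragraph and a less favourable power statement. It makes the claim honest but does not restore 80%; that needs more employees, more companies or acceptance of a larger detectable difference.

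Spreading the same employees over more companies would raise power without extra participants, but it is a trade-off, not part of the required correction. The plan invites every employee found to be at increased risk, and companies must be large clients of one insurer in three cities and give a letter of commitment. Whether enough such companies exist is not stated.

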**Figure 1 F1:**
[figure not shown]
Flow diagram of participant recruitment.

### Intervention group

The wellness specialists will calculate the adapted Framingham score for all employees who have voluntarily participated in their worksite’s wellness day. All employees who are identified as being at increased risk will receive a telephone call from the wellness specialist inviting them to participate in the research study. Should they agree, the wellness specialist will book the first face-to-face session, which will take place at the employee’s worksite.

Individuals in the intervention group will receive the same advice and health promotion materials as those in the control group. Additionally, they will be offered an individually tailored intervention that consists of one-on-one counselling sessions. The first intervention group will receive the six one-on-one counselling sessions over a 6-month period (6-I), while the second intervention group will receive the counselling over a 3-month period (3-I).

### Control group

The employees in the control group will receive usual care. This is comprised of feedback at the health and wellness day, directing employees to their physician if needed, and encouragingthem to increase their level of physical activity and to improve nutrition in a generic way. They will receive general health promotion material detailing the risks for cardiovascular disease and once-off advice on improving lifestyle behaviour. The participants from the control companies will also participate in follow up measurements at 6 and 12 months.

If the intervention is shown to be effective, the companies who were in the control group will receive the intervention after completion of the research study. Therefore, the control group will be wait-listed for the intervention.

### Outcome measures

The primary outcome of this study is a change in level of habitual daily physical activity. Secondary outcomes include: changes in dietary intake and Body Mass Index. Further, the secondary outcome measures include changes in the cardiovascular disease risk profile, which will be defined by the adapted Framingham score, incorporating blood pressure, total blood cholesterol, and smoking status. Data will be collected at baseline and at 6 and 12 months.

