## Background

Like many developing nations, South Africa has a dual burden of disease with non-communicable disease (NCD) accounting for more than a third (37%) of all death [1]. The other major causes of death are HIV/AIDS (30%) and other communicable diseases (21%) [1]. In addition to the increasing prevalence of NCD mortality and morbidity, there is a concomitant increase in the prevalence of contributing risk factors such as inactivity and obesity [2].

Indeed, South African employees are at increased risk for cardiovascular disease with more than half not meeting recommended physical activity guidelines [3]. Similarly, Prochaska et al., 2009 reported that 71% of the employees studied were inactive [4]. Furthermore, 80% of the employees were categorised as being at risk for 2 behavioural risk factors (which included inactivity, overweight or obese, smoking, not managing stress effectively) while 18% had three behavioral risks [4]. The workplace has been identified as a setting that can potentially reach a large number of people simultaneously, and positively impact on the risk and health profile of individuals [5,6], and is therefore an opportune setting for interventions targeting the adult population.

A health risk assessment (i.e. screening) has been regarded as an entry point in comprehensive health promotion programs and precedes the implementation of targeted interventions [7][8]. Those individuals identified as being at risk for cardiovascular disease may therefore be directed to appropriate intervention programs [9] aimed at reducing future healthcare expenditure. Interventions targeting those categorised as ‘high risk’ or ‘moderate risk’ [7] are likely to show greater improvements in health [9]. This is supported by Groeneveld et al., (2010) who conducted a recent review and reported that the health benefits from worksite interventions for employees who were not at risk for cardiovascular disease were minimal, compared to those employees identified as being at risk who showed greater improvements [10].

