### Step 5: Adoption and implementation plan

#### Pilot study

A pilot study was conducted in a convenient sample of employees for 12 weeks. The aim of the pilot was to determine the feasibility of the interventions and also to allow the counsellors to gain experience and proficiency in motivational interviewing techniques.

Eight wellness counsellors, based in three different South cities, recruited a convenience sample of both male and female employees (n = 225). The baseline participant characteristics are presented in Table 2. Despite the mean serum cholesterol and blood pressure being within normal ranges, more that 80% of the employees volunteering to participate had two or more risk factors for cardiovascular disease.

**Table 2 T2:** Baseline characteristics of participants in the pilot study

	**n**	**Mean**	**± Standard Deviation**
Age (years)	225	40.0	10.8
Men (% of total sample)	121	51%	
Body Mass Index (kg/ht2)	225	31.0	5.5
Cholesterol (mmol/l)	228	4.7	0.9
Diastolic Blood Pressure (mm Hg)	229	84.1	11.6
Physical Activity (min/wk)	225	63.0	120.9

The analysis of covariance (ANCOVA) was performed to measure the effectiveness of the 12-week intervention. Participants were grouped into being either at risk or not at risk for each of the individual risk factors, and then the baseline and follow up measures were compared for each specific risk factor. Diastolic blood pressure decreased significantly over the 12 weeks period among those whose baseline result placed them in the at risk group (Diastolic blood pressure more than 90 mmHg) from 95.8 mmHg ± 9.8 to 90.1 mmHg ± 13.7 (p < 0.0001). Similarly, those with 2 or more risk factors at baseline decreased their number of risk factors from 3.5 ±0.8 to 3.0 ± 1.0 at follow up (p < 0.0001). In addition, there was a significant group and time effect for Body Mass Index, where those who were overweight or obese (BMI >25) at baseline experiencing a slight decline at 12 weeks (data not shown). This is an encouraging finding as 83% of the participants were either overweight or obese at baseline.

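### The 80% power is for a comparison of proportions meeting the activity guideline, but the stated primary outcome is a change in activity level tested by ANOVA

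*Protocol article*

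**What the plan says.** **Outcome.** The Outcome measures section says: "The primary outcome of this study is a change in level of habitual daily physical activity". It gives no metric and no primary time point; data are collected at baseline, 6 and 12 months.

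**Sample size.** The Sample size calculation section says: "The sample size was determined according to a power calculation using a dichotomous variable: meeting the PA guideline". The rates are "at baseline 50% not meeting the guideline and after the intervention 40% (intervention group) vs 50% (in control group", with "80% power and significance of 0.05". The result is that "775 employees are required at the 12-month follow-up with 387 in control group and 387 in intervention group".

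**Measurement.** The Habitual physical activity section sums the questionnaire domains to total minutes per week. It also plans to classify participants by whether they reach 150 minutes.

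**Analysis.** The abstract and the Statistical analyses section name one test for changes in physical activity, an ANOVA at 6 and 12 months. In Statistical analyses, proportions appear only in frequency tables of the percentage at risk. The cost-effectiveness ratio uses a difference in mean activity levels.

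**Base rate.** In the Pilot study section, Table 2 has the row "Physical Activity (min/wk") with n = 225, mean 63.0 and SD 120.9. The Background reports that more than half of South African employees miss the guideline, and cites a study in which "71% of the employees studied were inactive".

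**The concern.** A power statement is a property of one endpoint and one test. Here the endpoint and test used for the power are not those given for the primary outcome. Two things follow.

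- The reader cannot tell what effect on activity level the trial can detect, because no difference or SD is stated for it.
- The share reaching 150 min/week and the mean change in minutes can lead to different conclusions. A few very active people can move the mean while the share hardly changes, and small gains around the cut-off can do the reverse. With both scales collected at both 6 and 12 months and none named as primary, the choice could be made after the data are seen.

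A smaller question is whether 50% is a sound base rate, given how low activity was in the pilot.

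**Working it through.** **1. Reproduce the stated sample size.** Inputs from the Sample size calculation section: p1 = 0.50, p2 = 0.40, power 80%, alpha 0.05. Sidedness is not stated; two-sided is assumed. The mean proportion is 0.45.

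n per group = [1.960 × √(2 × 0.45 × 0.55) + 0.8416 × √(0.25 + 0.24)]² / 0.10² = (1.379 + 0.589)² / 0.01 ≈ 387.3, so 388 when rounded up.

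Power at 387 per group = Φ[(0.10 × √387 − 1.379) / 0.700] = Φ(0.840) = 79.97%.

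The figure reproduces. Variants fit less well: 385 with unpooled variance, 408 with a continuity correction, 305 one-sided. The 80% is therefore that of a two-sided test of two independent proportions.

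**2. What the same numbers give for minutes per week.** The article states no target difference and no SD of change. Assumption: the pilot baseline SD of 120.9 applies, with 387 per arm and no clustering.

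Detectable difference at 80% power = (1.960 + 0.8416) × SD × √(2/387).

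- Comparing follow-up values, SD = 120.9: 2.8016 × 120.9 × 0.0719 ≈ 24.3 min/week, which is 0.20 SD and 24.3/63.0 = 39% of the pilot mean.
- Comparing change, SD = 120.9 × √[2(1 − r)], where r is the baseline-to-follow-up correlation:

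| r | SD of change | Detectable difference (min/week) |
|---|---|---|
| 0 | 171.0 | 34.4 |
| 0.3 | 143.1 | 28.8 |
| 0.5 | 120.9 | 24.3 |
| 0.7 | 93.6 | 18.9 |

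With SD 120.9, power is 21% for a true difference of 10 min/week, 41% for 15, 63% for 20, 82% for 25 and 93% for 30. So the power for the stated outcome may lie well below or above 80%; the article does not give what is needed to say which.

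**3. The base rate and the pilot.** Minutes cannot be negative, so the share with at least 150 is at most mean/150 = 63.0/150 = 42% (Markov's inequality). At least 58% of the pilot sample was below 150, whatever the distribution. A 50% rate would need a mean of at least 0.50 × 150 = 75.

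Power with 387 per arm at other base rates (58% is the pilot bound, 71% the inactivity figure in the Background, 85% an illustration):

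| Not meeting, control | 10-point drop | Odds ratio of 1.5 held |
|---|---|---|
| 50% | 80.0% | 80.0% |
| 58% | 79.7% | 80.2% |
| 71% | 83.7% | 75.6% |
| 85% | 93.7% | 57.5% |

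The odds ratio of 1.5 is the one implied by 50% v 40%: (0.60/0.40) / (0.50/0.50). The protocol itself states only the two percentages, a 10-point difference.

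**The case against.** **The dichotomy is planned.** Participants will be classified at 150 min/week, and Step 2 of the intervention mapping makes reaching that level an objective. A reader might infer that the power calculation belongs to no analysis the investigators intend. The article does not support that. A test of the category may stand in a fuller protocol or an analysis plan, and an ANOVA run on a yes/no indicator would behave much like the two-proportion test at this size. What stands is that the article states the outcome, the test and the basis for power, and that these do not match.

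**The 50% has a visible source.** The Background and the literature review both report more than half of South African employees below the guideline, although that is a floor and not an estimate. The pilot was a convenience sample, its activity instrument is not named, and the trial's entry rule is not said to have been applied. The 95% interval for the pilot mean is 63.0 ± 1.96 × 120.9/√225, about 47 to 79, which includes the 75 that a 50% rate would need. The 58% bound describes the pilot sample and does not show 50% to be wrong for the trial.

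**Low power is not shown.** A reader might take the 57.5% above as the real power. It needs both an 85% base rate, which comes from fitting a skewed distribution to the pilot, and a constant odds ratio that the protocol never states. For the stated 10-point effect, power stays at about 80% or rises.

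**Skew does not invalidate the ANOVA.** An SD 1.9 times the mean points to strong right skew. However, a simulated two-group comparison of raw minutes at 387 per arm, without clustering and with no true effect, gave type I error of 5.0% (gamma shape) and 4.8% (lognormal shape). Skew costs efficiency here, not validity.

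**Conclusion.** The mismatch is real and rests on the article's own text. The 80% power is correct for a two-proportion test of meeting the guideline, but it does not belong to the primary analysis as stated, an ANOVA of change in activity level. One of two scales and one of two time points still has to be declared.

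The size of the consequence cannot be fixed from the document. Under the assumed pilot SD and 387 per arm, minutes per week have 80% power for about 24 min/week, or 19 to 34 for change at correlations from 0.7 to 0. Clustering by company is not included in any of these figures.

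The base rate is a secondary point. At least 58% of the pilot sample missed 150 min/week, so 50% deserves a check. The documents do not establish that 50% is wrong for the trial population or that the trial is underpowered.

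**What to change.** **Preferred.** Name one primary endpoint that matches the sample size: the proportion meeting 150 min/week at 12 months, intervention v control. State a baseline-adjusted binary-outcome model that respects company randomisation, such as a mixed logistic model or GEE by company. Make minutes per week, and the 6-month results, secondary. The price is some information lost by dichotomising, which keeping minutes as secondary partly recovers.

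**Alternative.** Keep change in minutes per week as primary at one named time point. State the target difference, the SD and the assumed correlation, and restate the power for that comparison.

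**In either case.** Tabulate the share below 150 min/week from the pilot data already held, and show power over a range of base rates (or SDs) in place of the single 50%.

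The cost is a few sentences of protocol wording and one recalculation, with no new data. It should be done before outcome data are compared between groups.
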